## Hypothesis

(1) There are differences in functional outcome [differences of more than 10 points using the Harris Hip Score (HHS): [18]] and the Visual Analog Score [VAS: difference of more than 10 mm [19]] between the treatment groups (HA and CS infiltration) and the control group (Bupivacaine) in favour of the treatment groups, at 6 months follow-up in the treatment of symptomatic hip OA patients.

(2) There are differences in secondary outcome measures [Hip disability and Osteoarthritis Outcome Score (HOOS) [20]] between the treatment groups and the control group in favour of the treatment groups, at 6 weeks, 3 and 6 months follow-up in the treatment of symptomatic hip OA patients.

(3) There are differences in functional outcome and the VAS between the treatment groups and the control group in favour of the treatment groups, at 6 weeks and 3 months follow-up in the treatment of symptomatic hip OA patients.

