### Planned Statistical Analysis & Sample size calculation

A linear regression model for repeated measures will be used to compare the evolution of the scores between the groups. More specifically, a direct likelihood approach will be adopted using an unstructured covariance matrix for the repeated measures (Molenberghs and Kenward, 2007, Section 14.4). The approach has the advantage that less stringent assumptions are made, not only with respect to the covariance structure, but also to the mechanism underlying the missing observations. The approach does not assume that all variances or all covariances will be equal (as is done in classical repeated-measures ANOVA or in a mixed model using only a random subject effect). Furthermore, the approach allows that the missingness depends on the observed values (the so-called missing at random assumption (MAR)), whereas an analysis restricted to patients with complete information assumes the missingness to be completely at random (MCAR) (G. Molenberghs and M.G. Kenward)[45].

The primary analysis is based on intention-to-treat, i.e. all patients who received an infiltration at baseline are included. Appropriate transformations will be considered if needed to meet the statistical assumptions of the regression model. Time point-specific comparisons between the groups of the changes with respect to baseline will be made based on this model. Confidence intervals (CI) of the change as well as the difference (at each timepoint) between groups will be constructed. To protect against an inflated type-I error (due to the presence of two outcomes and two pairwise comparisons), an alpha-level of 0.01 will be used for each comparison with respect to the control group (Bonferroni correction).

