A sample size calculation was performed to have at least 80% power to detect in both groups compared with placebo, a clinically meaningful difference in change (baseline-6 months) of 10 mm in VAS and 10 points in HSS. The SD of HSS and VAS is assumed to be equal to 16 and 20 respectively. Estimates are obtained from Frihagen et al. [46] and Qvistgaard [15]. Assuming a moderate correlation of 0.5 between the measurement at baseline and after 6 months, a total of 285 patients are needed, i.e., 95 subjects in each group. With this sample size, 80%power is achieved for VAS and 96.2% for HHS. The number of included subjects will be increased by 10% to compensate for the loss of power due to patients with missing observations (therefore, 105 patients per group will be recruited). Interim analyses are planned after 1/3 and 2/3 of the patients included reach the end of the follow-up period to allow for an early stopping of the study (or accrual of patients in a specific treatment group) due to rejection of the null hypothesis. Using the O'Brien-Fleming method (O'Brien and Fleming 1979) results in respectively |4.495|, |3.178| and |2.595| as critical values for the Z-statistic at the three analysis time points. Otherwise stated, p-values are declared significant if they reach p < 0.000007, p < 0.00148 and p < 0.0095 at the first interim analysis, the second interim analysis and at the final analysis, respectively. (Note that the 'price to pay' for performing the interim analysis is a slightly more conservative alpha-level at the final analysis, i.e. alpha = 0.0095 instead of alpha = 0.01)

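### The 80% power stated for an effect in both active groups is the power of each VAS comparison with control taken alone; for both VAS comparisons together it is about 69%

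*Protocol article*

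**What the plan says.** All of the following is in the protocol article. Under Planned Statistical Analysis & Sample size calculation, the aim is given as "at least 80% power to detect in both groups compared with placebo, a clinically meaningful difference", and the target is a "difference in change (baseline-6 months) of 10 mm in VAS and 10 points in HSS" (HSS there means the Harris Hip Score, HHS). The same paragraph arrives at "a total of 285 patients are needed, i.e., 95 subjects in each group" and reports power by outcome, 80% for VAS and 96.2% for HHS. Recruitment is then raised to 105 per group to allow for missing observations.

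On multiplicity, the section says "an alpha-level of 0.01 will be used for each comparison with respect to the control group (Bonferroni correction"). The first entry under Hypothesis expects differences "between the treatment groups (HA and CS infiltration) and the control group (Bupivacaine) in favour of the treatment groups, at 6 months follow-up", so it names both products. No power figure for the two products together is given anywhere.

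**The concern.** Read literally, the sentence attaches the 80% to the event that HA and CS both beat control. The two figures reported after it are per-comparison figures, and the probability that two tests both succeed is lower than the probability for either one unless they are perfectly correlated.

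At stake is how the results are read. Someone who takes the 80% as joint would expect at least one VAS comparison to miss in no more than 20% of trials when both products work as assumed. The plan's own inputs make that about 31%. A split result, with one product significant and the other not, would then look more surprising than it should.

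**Working it through.** **Inputs, all from the sample size section**
- Difference to detect: 10 mm on VAS and 10 points on HHS.
- Spread: "The SD of HSS and VAS is assumed to be equal to 16 and 20 respectively".
- Correlation: "Assuming a moderate correlation of 0.5 between the measurement at baseline and after 6 months".
- Evaluable patients: 95 per group, equal allocation.
- Critical values: "4.495|, |3.178| and |2.595| as critical values for the Z-statistic at the three analysis time points". They are limits on the absolute Z, so the tests are two-sided. The final limit is 2.595; without interim looks, 0.01 two-sided gives 2.576.

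**Step 1. Reproduce the plan's figures (one comparison)**
- SD of change = SD × √(2(1 − r)). With r = 0.5 this equals the SD itself: 20 for VAS and 16 for HHS.
- VAS: standard error = 20 × √(2/95) = 2.902; expected Z = 10/2.902 = 3.446; power = Φ(3.446 − 2.595) = Φ(0.851) = 80.3%. At limit 2.576 it is 80.8%; a t test at 0.01 gives 79.95%.
- HHS: standard error = 16 × √(2/95) = 2.321; expected Z = 4.308; power = Φ(4.308 − 2.595) = 95.7%. At limit 2.576 it is 95.8%.

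The stated 80% for VAS is reproduced, and the stated 96.2% for HHS to within about half a point. Both are single-comparison powers.

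**Step 2. Power for both VAS comparisons**

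Each comparison uses the same control mean. With equal groups, the covariance of the two differences is σ²/n and each variance is 2σ²/n, so the correlation is 0.5. Joint power is the probability that two standard normal variables with correlation 0.5 both fall below 0.851.

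| Setting | Each VAS comparison | Both VAS comparisons |
|---|---|---|
| 95 per group, limit 2.595 | 80.3% | 69.1% |
| 95 per group, limit 2.576 | 80.8% | 69.8% |
| 105 per group all evaluable, limit 2.595 | 84.8% | 75.5% |

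A simulation of the three-look design with the stated limits gave about 69.4% for both, so the interim looks do not close the gap. Nor does the 10% inflation: those patients are meant to replace missing data, and with none missing the joint figure is still below 80%. A joint 80% on VAS would need 113 to 114 evaluable patients per group.

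**Step 3. Related quantities at 95 per group, limit 2.595**
- At least one VAS comparison significant: 2 × 0.8026 − 0.6908 = 0.914, about 91%.
- At least one of the two missed: 1 − 0.691 = 31%.
- A given product missed: 1 − 0.803 = about 20%.
- Both HHS comparisons: about 92%, so HHS alone raises no problem.
- All four primary tests: about 64% to 69% for a VAS–HHS correlation of 0 to 0.8. The protocol gives no such correlation, so that range is an assumption.

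**Step 4. Common baseline mean**

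If the baseline means are constrained equal across the randomised groups, the relevant SD is about 20 × √(1 − 0.5²) = 17.32. Then the standard error is 17.32 × √(2/95) = 2.513 and the expected Z is 3.979. Power is Φ(3.979 − 2.595) = 91.7% per VAS comparison and 85.9% for both.

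**The case against.** The strongest reply is that 'both' means 'each of the two'. Three features of the plan support it. Alpha is set for every comparison with control separately. Power is reported separately for VAS and HHS. Accrual may be stopped in a single treatment group, which implies that each product is judged on its own. A Bonferroni split is also what separate claims require. A rule that all comparisons must succeed would need no split, and at two-sided 0.05 the same inputs give 88% for both VAS comparisons. On this reading the 80% and the 95 per group agree. All of this stands. What it leaves untouched is that the sentence does not say 'each' and that no joint figure is offered.

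A reader might infer three stronger things, none of which the document supports:
- **That the sample size is wrong.** It is not: 95 per group delivers the stated power per comparison.
- **That the trial succeeds only if both products, or all four tests, are significant.** The protocol states no such rule, so 69% is not the power of a declared success criterion.
- **That a given effective product would be missed in about three trials out of ten.** The 31% is the chance that at least one of the two is missed. For a given product the figure is about 20%, as the stated 80% implies.

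**Conclusion.** The point holds as an ambiguous power statement that is overstated on its literal reading. The literal claim falls short by about 11 percentage points on VAS (69% against 80%); the per-comparison claim is correct. The joint figure rests on the plan's own SD, correlation, effect and limit, on equal group sizes with 95 evaluable in each, and on both products having exactly the assumed 10 mm effect. No test, threshold or sample size is invalidated.

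**What to change.** Replace the power sentence with one that says what was calculated: 80% power for each VAS comparison with control, 96% for each HHS comparison, and about 69% for the two VAS comparisons jointly. This costs one sentence and no patients; the only price is a less favourable joint figure in print.

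Optionally, constrain the baseline means to be equal across the randomised groups in the repeated-measures model already planned, and state about 92% per VAS comparison and 86% for both. This also needs no extra patients. It does alter how the between-group contrast in change is estimated, and its gain depends on the assumed correlation of 0.5, so it should be prespecified. It is an improvement to the analysis; the sentence needs restating in either case.

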#### Primary outcomes

Assessment of group differences at 6 months for:

• Harris Hip Score (HHS) [18]: this score will be used as a self-administered questionnaire in accordance with the developers' instructions. The Harris Hip Score was first developed in 1967 and is accepted as one of the best used questionnaires dealing with hip function. It is a disease-specific scoring system which was introduced to provide an evaluation system for various hip disabilities and methods of treatment. This Score gives a maximum of 100 points, with domains of pain, function, deformity and motion. Pain and function are the two basic considerations and receive the heaviest weighting (44 and 47 points, respectively). Range of motion and deformity are seldom of primary importance and therefore receive five and four points, respectively. Function is subdivided into activity of daily living (ADL, 14 points) and gait (33 points).

• Visual Analog Score (VAS) [19]: this score is a self-assessment of variation in pain intensity, measured on a simple 100-mm-long continuous scale of absolutes ranging from 0 = "no pain" to 100 = "extreme pain". The percentage of pain is determined by physically measuring from the "0" end to the patients' mark on the pain scale and dividing this value by total length of the line. The advantage of the VAS is that you can determine the change in pain by taking the difference between any two recordings of pain severity.

#### Secondary outcomes

Assessment of group differences on:

• Hip disability and Osteoarthritis Outcome Score (HOOS) [20]: this score will be used as a self-administered questionnaire with the help of the developers' instructions. The HOOS is an adaptation of the Knee disability and Osteoarthritis Outcome Score (KOOS) intended to evaluate symptoms and functional limitations related to the hip. The HOOS consists of 40 items assessing five different patient-relevant groups: Pain (P) (ten items); Symptoms (S) including stiffness and range of motion (five items); Activity limitations-daily living (A) (seventeen items); Sport and Recreation Function (SP) (four items); and Hip Related Quality of Life (Q) (four items). The HOOS contains all Western Ontario and McMaster Universities Osteoarthritis Index (WOMAC) questions in unchanged form. The WOMAC scores are often used in scientific literature and it is important that if needed the WOMAC scores can be calculated from the HOOS questionnaire. To answer each question, five options are used (no, mild, moderate, severe, extreme). All items are scored from zero to four, and each of the five subscales will be calculated as the sum of the items included. The HOOS is transformed into a 0-100 worst to best score.

• VAS, Harris Hip Score: at all follow-up time points, except after 6 months

• Patient evaluation of treatment outcome: The patients will be asked to assess their status on a 3-point scale (worse, stable or better then at the time of enrollment).

• Intake of escape medication: The number of escape medication taken/day will be determined.

• Safety: All complications/adverse events will be evaluated and the relationship to the test product determined. When they have complications, patients will be seen in our department earlier than normal.

The above primary and secondary measure instruments will be assessed at the time of enrollment into the study prior to any injection (baseline), and then again at six weeks, 3 and 6 months after the injection. The six-month follow-up period for all patients will begin on the date the injection is administered.

### Ethical review committee and informed consent requirements

Ethical approval was necessary because this is a prospective randomized study. Ethical approval has been obtained from the ethical committee of the Catholic University, Leuven. Informed consent forms will be signed by the patients before inclusion into our study. If patients, after reading the patient information, have any questions about our study protocol, they can contact [name] or [name].

## Discussion

This study is primarily designed to evaluate the effectiveness of non-operative treatment of hip OA using HA and CS infiltrations. A comparison is made between HA, CS and bupivacaine (control group) infiltrations. There have been studies and even randomized clinical trials on non-operative treatment of hip OA but the methodological quality is often poor. There is a need for more rigorously designed studies on hip OA treatment as this subject is still very much under debate. By publishing our protocol we wish to share the robust design and methodological quality of our protocol. Moreover, when the design of a study is published it will help to achieve transparency about why and how studies are undertaken. The publication of a study design may help to reduce the problem of publication bias, i.e. selective publication of positive associations and disregarding negative and weak associations, prevent unnecessary duplication of research efforts and duplicate publication. To our knowledge, there has never been a similar study design published on the same subject. By making this study design available we wish to contribute to a more in-depth research on non-operative treatment of osteoarthritis of the hip and prevent publication bias for this double blinded randomized trial. Results of the trial will be disseminated through publication in relevant peer-reviewed journals and conference proceedings.
